## 6.2 Safety variables

### 6.2.1 Ocular tolerance

Objective ocular tolerance will be assessed in each eye at each visit, by an examination of the eye with the slit lamp. This examination will be performed without fluorescein or dye on each visit.

Slit lamp examination results will be recorded as normal or abnormal. Abnormalities will be described in the case report form. If any abnormality is noticed which was either not present at baseline or which is worse than at baseline, then the investigator will have to complete an adverse event form .

A precise evaluation of the lens opacity will be performed through the dilated pupil, using the LOCS II scale (appendix I.F).

### 6.2.2 Systemic tolerance

Fasting plasma lipoproteins profile [triglycerides (TG), total cholesterol (TC), HDL-C and

LDL-C] will be performed on D0, at the 6 month visit and at the 3 year visit. To this end blood samples after fasting will be taken. The protocol for dosage is described in appendix I.D. If any abnormality is noticed which was either not present at baseline or which was worse than at baseline, then the investigator will have to complete an adverse event form .

Moreover, all systemic adverse events, particularly digestive adverse events (nausea, eructations, diarrhea or abdominal pain) and bleeding events*, will be registered all along the study (see paragraph 6.2.3).

** because there is no simple, specific and accurate biologic index allowing to predict the risk for bleeding.*

### 6.2.3 Adverse or unexpected events

Adverse or unexpected event occurring during the study (from the time of patient inclusion to that of withdrawal or completion ) should be reported regardless of whether the event is attributed or not to the study medication.

The onset of any event is recorded on the case report form at each visit. The complete description and characteristic of each event is recorded in the adverse events section at the end of the case report form.

In order to avoid bias in the patient’s answers, general questions with no hint of suggestion must be used.

If an event is serious, a complementary report of a serious adverse event form (last page of case report form) must be completed and transmitted to the sponsor as soon as possible.

The sponsor and the Study Manager or the Clinical Research Assistant are to be notified of any serious adverse event by telephone (N° [name] or [name]) or by fax (N° [name]) or by e-mail ([contact]).

A serious adverse event or serious adverse drug reaction is defined by ICH guidelines as "Any untoward medical occurrence that at any dose : results in death, is life-threatening, requires inpatient hospitalisation or prolongation of existing hospitalisation, results in persistent or significant disability/incapacity, or is a congenital /birth defect".

The sponsor is responsible for the prompt notification of serious adverse effects to the Ethics Committee. The investigator shall supply the sponsor and the Ethics Committee with any additional requested information, notably for reported death of a subject.

If the name of the study treatment must be known in order to treat a serious reaction, the code can be broken according to the procedure defined in section 5.4.

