### 4.3.3 Removal of patients from therapy or assessment

If a patient did not attend a scheduled control visit, he/she will be contacted again. In case of premature withdrawal from the study, the investigator is to make every effort to determine the reason.

Generally, patients may withdraw or be withdrawn from the study for the following reasons:

- Patient’s decision (in accordance with the Declaration of Helsinki, any patient can voluntarily discontinue the study at any time he or she chooses, without prejudice).
- If the investigator considers that the patient’s health is compromised by remaining in the study.
- If the patient is not sufficiently co-operative.
- If a serious adverse event prevents the patient from attending the follow-up visits.

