## 5.4 Randomisation and code-breaking

The randomisation list will be prepared prior to the enrolment using the QL-Ranclin software.

Treatments will be balanced in a 1 to 1 ratio.

At the end of the baseline visit (Day 0), patients who fulfilled all inclusion criteria and none of the exclusion criteria will be randomly assigned to one of the treatment groups (DHA or placebo).

Only in emergencies, and for reasons which must always be given, can the code be broken.

For this purpose sealed opaque envelopes, bearing the number of the patient and containing the name of the allocated treatment, will be given to the investigator or the pharmacist.

It is thus possible to unmask the treatment of one patient only without unmasking all the others.

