### 6.1.2 Examination schedule

The different visits will take place on D0, Month 6 (15 days), Year 1( 30 days),

Year 2 (30 days) and Year 3 ( 30 days).

Before inclusion, a baseline assessment will take place on D0. Besides validating the inclusion and exclusion criteria, this baseline visit will also enable the recording of demographic (including ethnicity) and baseline data. Data concerning some identified risk factors for AMD, as age and history of addiction to smocking, will be recorded. Moreover a diet questionnaire must be completed in order to assess the patient’s fish intake frequency.

Any general pathology (particularly diseases predisposing to bleeding or haemorrhage) and ocular pathology as well as any concomitant treatment will be recorded.

These data will be updated all along the study.

For patients previously supplemented with omega-3 fatty acids the corresponding stopping date will be recorded.

On each visit, ophthalmic assessments will include the following:

- Best corrected visual acuity measured with ETDRS charts
- Slit Lamp Examination
- Multifocal ERG (except on 6 month visit)
- Fundus photographs
- Fluorescein angiography (except on 6 month visit)

Moreover a complete profile of blood lipids will be performed on D0, at the 6 month visit and at the 3 year visit : fasting plasma lipoproteins [triglycerides (TG), total cholesterol (TC), HDL-C and LDL-C ] and fatty acids in serum and in red blood cell membranes (RBCM) will be measured. To this end 15 ml of venous blood will be collected after a 12 hour fasting period (as described in appendix I.D).

These data will allow first to evaluate for each patient the compliance to the treatment (DHA level in plasma) and the efficacy of DHA to penetrate the cell membrane (DHA level in RBCM), then to confirm the safety of the treatment concerning the metabolism of lipoproteins (fasting plasma lipoprotein profile).

Moreover since TC is considered as a risk factor for age-related macular degeneration, it will be considered for evaluation of treatment efficacy.

Furthermore, as previously mentioned (see section 4.2), apoE genotype of consenting patients will be evaluated on DNA of white blood cells, on D0.

10 ml of venous blood will be collected. The protocol for extraction of DNA from white blood cells and for evaluation of apoE allele is given in appendix I.E. If appropriate, the efficacy of the treatment will be assessed considering the apoE genotype .

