### 6.1.3 Assessments of efficacy variables

### Primary efficacy variable

The occurrence of choroidal new vessels in the study eye will be determined from prospective assessment of fluorescein angiography every year.

Patients will be asked to report any new visual symptoms referable to the study eye between visits and to come back immediately for an angiography. Then a suitable laser or photodynamic therapy will be performed if any CNV have occurred.

Fluorescein angiography will allow to detect the presence and specify the location (extrafoveal, juxtafoveal, subfoveal), type (classic, occult) of CNV. It will be performed, through the dilated pupil, after intra-venous injection of 10% sodium fluorescein. This examination will be performed first on D0 for both eyes, then yearly.

If CNV are suspected in the study eye, an indocyanine green (ICG) angiography will be also performed to confirm their occurrence and characterize them precisely.

The protocol for fluorescein and ICG angiography is described in appendix I.C.

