## 6.3 Study flow chart

| | **STUDY PROCEDURE** | **Visit 1** | **Visit 2** | **Visit 3** | **Visit 4** | **Visit 5** | | --- | --- | --- | --- | --- | --- | | **Baseline** | **6 months*** | **1 year**** | **2 years**** | **3 years**** | | Informed written consent | **X** |  |  |  |  | | Demographic data | **X** |  |  |  |  | | Medical history- Concomitant pathologies and treatment | **X** |  |  |  |  | | Inclusion criteria | **X** |  |  |  |  | | Diet questionnaire | **X** |  |  |  |  | | Blood samples ****  *12h fasting* | **X**  25 ml | **X**  15 ml |  |  | **X**  15 ml | | Visual acuity (ETDRS) | **X** | **X** | **X** | **X** | **X** | | Slit Lamp Examination | **X** | **X** | **X** | **X** | **X** | | Multifocal ERG **** | **X** |  | **X** | **X** | **X** | | Fundus Photographs | **X** | **X** | **X** | **X** | **X** | | Fluorescein angiography  (+/-ICG angiography) | **X** |  | **X** | **X** | **X** | | Adverse event report |  | **X** | **X** | **X** | **X** | |
| --- | --- | --- | --- | --- | --- | --- | --- | --- | --- | --- | --- | --- | --- | --- | --- | --- | --- | --- | --- | --- | --- | --- | --- | --- | --- | --- | --- | --- | --- | --- | --- | --- | --- | --- | --- | --- | --- | --- | --- | --- | --- | --- | --- | --- | --- | --- | --- | --- | --- | --- | --- | --- | --- | --- | --- | --- | --- | --- | --- | --- | --- | --- | --- | --- | --- | --- | --- | --- | --- | --- | --- | --- | --- | --- | --- | --- | --- | --- | --- | --- | --- | --- | --- |

**** not part of usual follow-up for AMD * Schedule  15 days

** Schedule  30 days

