## 8.2 Determination of sample size

The primary criterion is the time to occurrence of choroidal new vessels (CNV) in the study eye.

The occurrence rates of CNV in both treatment groups will be compared using a log-rank test.

According to previous studies (24) the 3 year risk of developing CNV in one eye is about 30 % (10% per year) for patients with CNV in the fellow eye.

Based upon expectation that DHA-treatment should reduce this rate to 15% at 3 years after D0 , sample size was thus performed assuming a 3 year CNV risk for the study eye in the treated group and in the placebo group to be 15% and 30% respectively.

The number of patients has been calculated with the Pass software for survival curves according to the following hypotheses:

- 2 tailed test
- Type I error  = 0.05
- Type II error  = 0.20 (80% power)
- Regular recruitment and Inclusion period: 1 year
- Follow up period per patient : 3 years
- Equal proportion of patients in each treatment group
- Drop-out rate in each group : 20%

Based on the above specifications the total number of patients should be 245.

Data on 248 evaluable patients are to be available (124 per group).

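### The adverse-event window opens after the D0 procedures and closes at an undefined withdrawal, with no duty to follow serious events to their outcome

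*Protocol*

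**What the plan says.** Section 6.2.3 limits reporting to events occurring "from the time of patient inclusion to that of withdrawal or completion", whatever their suspected cause. Inside that window each event is recorded and described in the case report form. A serious event also needs a separate form sent promptly to the sponsor. The investigator must give the sponsor and the Ethics Committee further information when asked, with a reported death singled out.

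On the start of the window:
- Section 6.1.2: "Before inclusion, a baseline assessment will take place on D0".
- Section 6.1.3, on fluorescein angiography: "This examination will be performed first on D0 for both eyes, then yearly". The same section describes a multifocal ERG with a contact-lens electrode on an anaesthetised cornea.
- Section 5.4: "At the end of the baseline visit (Day 0), patients who fulfilled all inclusion criteria and none of the exclusion criteria will be randomly assigned".
- Section 6.3 (flow chart): the row "Adverse event report" is blank at Visit 1 and marked at Visits 2 to 5. Blood sampling (25 ml at Visit 1) and multifocal ERG, but not angiography, carry the note "not part of usual follow-up for AMD".

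On the end of the window:
- Section 4.3.3 lists as a reason for withdrawal: "If a serious adverse event prevents the patient from attending the follow-up visits". Section 9.2 repeats it, and asks for the date, the reason and, where possible, a view of the therapeutic response.
- Section 8.1 wants time to CNV where possible from patients who stop medication early, and censors patients withdrawn early at that point. It also promises a full account of every serious event with a detailed patient profile.

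**The concern.** A reporting window decides which harms the sponsor and the Ethics Committee must hear about, so both ends need to be in the right place.

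At the start, the study asks patients to undergo an injection, a corneal-contact examination and blood sampling before the window opens. The protocol itself treats dye allergy as a known risk: it is an exclusion criterion in section 4.3.2 and a contraindication in Appendix I.C. For a patient who reacts at D0 and is then not randomised, section 6.2.3 gives no reporting route.

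At the end, a serious event can itself cause withdrawal, and withdrawal closes the window. The patients whose later course matters most for safety may then be those for whom nothing further is required. Section 6.2.2 adds weight: it says no simple laboratory index predicts bleeding risk, so that signal depends on clinical reporting.

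**Working it through.** The plan gives no figure to reproduce. The check is to set the rules side by side.

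**Start of window**
1. Reporting opens at inclusion (6.2.3).
2. The D0 baseline assessment comes before inclusion (6.1.2).
3. That assessment contains fluorescein angiography, multifocal ERG and blood sampling (6.1.2, 6.1.3, 6.3).
4. Randomisation follows at the end of the visit, once eligibility is settled (5.4).
5. Visit 1 has no adverse-event report (6.3).

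So an immediate reaction to a D0 procedure occurs before the window opens and has no scheduled place to be recorded. A reaction that starts after inclusion is inside the window and can be recorded at Visit 2. Angiographies are scheduled at D0, Year 1, Year 2 and Year 3, so 1 of 4 (25%) precedes the window. That is a share of injections, not of reactions.

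**End of window**
1. A serious event that prevents attendance may lead to withdrawal (4.3.3, 9.2). The event happens before the withdrawal, so it is inside the window and is reported with a serious-event form (6.2.3).
2. After that, section 6.2.3 requires further information only on request. Section 9.2 names no adverse-event follow-up, and no section requires following an event to resolution.
3. An event that starts after withdrawal is not reportable.
4. Section 8.1 nevertheless promises a complete account of serious events. If the outcome comes after withdrawal and nobody asks for it, that account is incomplete.

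**Meaning of withdrawal**
Sections 4.3.3 and 9.2 speak of leaving the study. Section 8.1 also speaks of withdrawal from medication, and seeks CNV data from those patients. Section 6.2.3 does not say which it means. If it means the study, a patient who only stops capsules stays under adverse-event reporting. If it means medication, efficacy collection continues in that patient while safety collection ends.

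**Illustration of person-time (not an estimate)**
Inputs: 248 patients, 3 years each, and section 8.2's "Drop-out rate in each group : 20" per cent.
- Planned person-time: 248 × 3 = 744 patient-years.
- Early leavers: 0.20 × 248 = 49.6.
- If exits are uniform over 3 years, each leaver loses 1.5 years on average: 49.6 × 1.5 = 74.4 patient-years; 74.4 / 744 = 10%.
- If all leave at the end, 0%; if all leave at once, 49.6 × 3 = 148.8 patient-years; 148.8 / 744 = 20%.

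The timing of exits is not in the document. The 20% is a planning assumption covering every reason for dropping out.

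**The case against.** The strongest reply is that the rule sorts events by when they occur and does not order follow-up to stop. A reader might infer that a patient withdrawn for a serious event leaves the safety record at that moment, and that a later death from it is lost. The text does not support that. The event is inside the window, must be reported and described, and further information must be supplied on request, with death named in particular. What remains is narrower: the duty depends on someone asking, and new events after withdrawal are outside it.

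A second reply is that D0 reactions come before randomisation and the first capsule. They cannot differ by arm because of treatment, and the safety population in section 8.1 contains only randomised patients who took study medication. This stands in full. The flow chart also implies that angiography is usual AMD care, and known reactors are excluded, which lessens the point for the injection. It does not remove it for the ERG and blood sampling, which the flow chart marks as outside usual follow-up.

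Third, the 10% of patient-years might be read as harm missed, or as concentrated in patients withdrawn for harm. Neither has a source. Sections 4.3.3 and 9.2 list other reasons for leaving, and some leavers would refuse contact under any rule.

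Finally, section 9.1 says assessments continue after a deviation unless the patient's condition requires stopping. That fits the study-level reading of withdrawal, but the exception covers the patients at issue here.

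**Conclusion.** The point holds in a limited form. As written, the window leaves immediate reactions to D0 procedures unreported, makes events starting after withdrawal non-reportable, and does not require a serious event leading to withdrawal to be followed to its outcome. The meaning of withdrawal in section 6.2.3 is unclear.

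The start-of-window gap concerns oversight of study procedures and has no effect on the treatment comparison. The end-of-window gap makes the safety description less complete; the document gives no ground to say that it falls unequally on the two arms. Sample size, power and the primary analysis are unaffected.

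This rests on two readings: that consent is signed before the D0 procedures, and that inclusion comes after the baseline assessment, as section 6.1.2 states. It is a protocol rule that a later analysis plan could not repair, because data not collected cannot be analysed. It is worth correcting because the correction is cheap.

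**What to change.** Amend section 6.2.3 as follows:
- Reporting starts at signature of consent, before any D0 procedure. Add Visit 1 to the adverse-event row of the flow chart in section 6.3.
- Withdrawal means withdrawal from the study, so patients who only stop capsules stay under adverse-event reporting.
- Serious events, and events leading to withdrawal, are followed until resolved or stable, including after withdrawal.
- Where the patient allows contact, early leavers are asked for vital status and serious events at their planned Year 3 date. Section 9.2 should say the same.

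A short reporting period after the last capsule is optional; its length is for the sponsor to set.

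The cost is amendment wording, one flow-chart mark and some telephone calls by the study nurse already named in section 7.1. Under the planning drop-out that is at most about 50 calls (0.20 × 248 = 49.6). Patients who refuse further contact will still be missing.

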## 6.3 Study flow chart

| | **STUDY PROCEDURE** | **Visit 1** | **Visit 2** | **Visit 3** | **Visit 4** | **Visit 5** | | --- | --- | --- | --- | --- | --- | | **Baseline** | **6 months*** | **1 year**** | **2 years**** | **3 years**** | | Informed written consent | **X** |  |  |  |  | | Demographic data | **X** |  |  |  |  | | Medical history- Concomitant pathologies and treatment | **X** |  |  |  |  | | Inclusion criteria | **X** |  |  |  |  | | Diet questionnaire | **X** |  |  |  |  | | Blood samples ****  *12h fasting* | **X**  25 ml | **X**  15 ml |  |  | **X**  15 ml | | Visual acuity (ETDRS) | **X** | **X** | **X** | **X** | **X** | | Slit Lamp Examination | **X** | **X** | **X** | **X** | **X** | | Multifocal ERG **** | **X** |  | **X** | **X** | **X** | | Fundus Photographs | **X** | **X** | **X** | **X** | **X** | | Fluorescein angiography  (+/-ICG angiography) | **X** |  | **X** | **X** | **X** | | Adverse event report |  | **X** | **X** | **X** | **X** | |
| --- | --- | --- | --- | --- | --- | --- | --- | --- | --- | --- | --- | --- | --- | --- | --- | --- | --- | --- | --- | --- | --- | --- | --- | --- | --- | --- | --- | --- | --- | --- | --- | --- | --- | --- | --- | --- | --- | --- | --- | --- | --- | --- | --- | --- | --- | --- | --- | --- | --- | --- | --- | --- | --- | --- | --- | --- | --- | --- | --- | --- | --- | --- | --- | --- | --- | --- | --- | --- | --- | --- | --- | --- | --- | --- | --- | --- | --- | --- | --- | --- | --- | --- | --- |

**** not part of usual follow-up for AMD * Schedule  15 days

** Schedule  30 days

# 7. QUALITY ASSURANCE

## 7.1 Study monitoring

Periodically a study promotor representative will contact the investigator and the study nurse* and will visit the centre. He/she will ensure that the study is progressing in compliance with the protocol, the local regulations and Good Clinical Practices.

The investigator will make the relevant clinical files available to the clinical study assistant who will maintain patient’s anonymity*.*

** the study is conducted in this centre in partnership with the CIC (Centre d’Investigation Clinique) of Créteil : a CIC study nurse will coordinate the study logistic in the centre.*

## 7.2 Data recording

The investigator is to ensure that all data are recorded on the case report forms as measurements are taken and examinations performed. Data are recorded by writing directly on the case report form or by transcribing from the patient’s original file.

The minimum data recorded in the patient’s original file will include: patient’s history and concomitant medication, patient’s inclusion in the study, all visit dates, summary of clinical condition with adverse events, date of study end or premature withdrawal with reason.

Each page of the case report form must be identified by the patient’s number and the investigator ‘s (or his/her representative’s ) signature (or initials).

Any correction must be dated and countersigned. Data are to be recorded with a ball-point pen.

## 7.3 Archives

Each page of the case report form is in triplicate, one is for the investigator’s archiving file and the other 2 are for the sponsor.

Likewise, the patient consent form is in triplicate. The first copy is kept by the investigator in the archive file, the second is kept by the sponsor in a sealed opaque envelope to maintain patient’s anonymity and the third copy is given to the patient.

All the study documents [list of patients included in the study, patient consents, case report forms and source documentation (including printed fundus photograps and digital images files saved on floppy or CD rom), signed protocol, investigator’s brochure and correspondence] must be archived according to ICH Guidelines.

## 7.4 Auditing / Inspection

During or after the study, the sponsor may carry out an audit of this clinical study. An auditor will be appointed by the sponsor.There may be regulatory inspection(s) and/or IEC reviews. All or part of the study related documents or source data will be verified to ensure that the standards of ICH Good Clinical Practices are met.

The investigator agrees beforehand to provide all the necessary documents and information for the audit (or inspection) to be performed.

